## Methods

### Study Design

To assess the working conditions of and burden on nurses in palliative settings, preliminary tests were executed to investigate the functionality of and user experience with wearables, including handling in a hospital environment and resistance to the hospital’s disinfection routines.

The study design (Figure 1), a prospective cross-sectional approach with continuous measurements throughout each workday, allows for assessing both the current manifestation of stressors and current level of perceived stress load both objectively and subjectively. Participants were split into groups, and each group conducted the measurements for 6 weeks, thus expanding the span of the measurement across all participants (to increase the time frame depicted in the data), while individual participants were not burdened with the additional workload for longer than necessary.

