In addition to these 2 questionnaires that were only completed once at the beginning of the measurements, the subjective stress level was also assessed throughout the workday and accompanied the continuous ambulatory measurements using EMAs. EMAs are short questionnaires asking for self-reported information that documents the perceived subjective experience of stress at a certain moment (ie, a *momentary* appraisal of their *current* stress level) [29]. The questionnaires popped up on the participants’ smartphones whenever an NFC tag was scanned that indicated the end of an activity (eg, end of rounds, leaving a patient room, end of a meeting, end of speaking with a patient or his or her relatives) and asked, for example, “How stressed do you feel right now?” with a continuous slider from 0% to 100%, labeled in increments of 20%. In addition, the questionnaire could also be accessed at any time by scanning a designated NFC tag called “open questionnaire.” Additional EMAs popped up when the participant put the setup on at the beginning of a shift (greeting the participant, asking for the subjective sleep quality of the night before, and asking about his or her current stress level) and when the setup was removed and shut down at the end of the shift (asking for the current stress level, asking how many patients were looked after throughout the day, and wishing the participant a pleasant recreational time).

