### Sample and Recruitment

The PCU at UMR, with its 14 beds, is the largest PCU in Mecklenburg-Western Pomerania, Germany. It employed 13 full-time nurses and 5 part-time nurses who work in a 3-shift system during the study implementation in 2021. Study participants had to be older than 18 years, their working time had to have a minimum of 20 hours per week, they had to have proficiency in written and spoken German, and they had to be employed at the palliative care unit at the Rostock University Medical Centre (inclusion criteria). Exclusion criteria comprised of nonconsenting capacity and nonfulfilment of all inclusion criteria. For the DiPa study, all 18 nurses working in the UMR PCU, who partly specialize in palliative care, were invited in December 2020 to participate in the study by presenting the procedure and aims of the project in a lecture as well as in a written inquiry. The measurement period for each participant was 6 weeks allowing for a total measurement duration of 3 months.

A power analysis was not conducted as the population was prespecified (N=18), rendering the need for an accruing sample. In the end, 12 nurses agreed to participate, resulting in a participation rate of 67% (12/18).

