The acceleration data were fused to a 3D vector by applying the following equation:

All algorithms for data extraction were written in Python using Jupyter Notebooks and the *Pandas*, *Numpy*, *SciPy*, *Matplotlib*, and *NeuroKit2* libraries.

For stress detection analysis, all stress events marked with a button press will be identified, and windows surrounding this event will be extracted and averaged, leading to one value per stress event per participant. Analogously, the windows surrounding a scan of the NFC tag “relaxation” and the baseline windows will be extracted and averaged as well. Descriptive and inferential statistical analyses will be applied using IBM SPSS Statistics 30. Weighted ANOVAs for correlated samples will be computed to compare the stressful events and the baseline for each physiological parameter.

To examine the predictability of experiencing stress, the subjective ratings given in the EMA will be used as ground truth. Surrounding the EMA, data windows will be extracted from the data for each physiological parameter. A linear regression will be computed with the subjective stress level (EMA) as the dependent variable and entering the means of the physiological variables (HR, HRV, tonic EDA, phasic EDA, temperature, and acceleration) as independent variables. Artificial intelligence approaches will be used to analyze the data where appropriate.

With the data for daily occupancy of patients and the total number of nurses on the same day, we will be able to calculate the relationships of these 2 variables with stress. The minimum occupation level according to the recommendation from the German Society for Palliative Medicine (*Deutsche Gesellschaft für Palliativmedizin*) on staffing in palliative wards [30] of 1.4 nurses per patient will be used as a cutoff to create two subgroups of “well-staffed” and “under-staffed.”

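### The regression of EMA stress ratings on physiology has no nurse term, so as written it treats repeated ratings from 12 nurses as independent and mixes between-nurse with within-nurse association

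*Protocol article*

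**What the plan says.** Under Data Analyses, the question of whether stress can be predicted is to be answered by one model: "A linear regression will be computed with the subjective stress level (EMA) as the dependent variable and entering the means of the physiological variables". The six predictors are HR, HRV, tonic EDA, phasic EDA, temperature and acceleration, each averaged over a window around the EMA. The row of the data set is therefore the EMA, not the nurse. No nurse or shift term, centring or clustered standard error is mentioned for this model. In the preceding paragraph, the comparison of button-press events with baseline is specified as ANOVAs for correlated samples.

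The data structure is given elsewhere:

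- Sample and Recruitment: "12 nurses agreed to participate". "The measurement period for each participant was 6 weeks".
- Procedures: measurements are to be made in every shift.
- Questionnaires: besides prompts at the start and end of a shift, an EMA opens "whenever an NFC tag was scanned that indicated the end of an activity".
- Strengths and Limitations: only the start and end prompts are mandatory. Those in between are optional and may be skipped.

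**The concern.** Ratings from one nurse resemble each other. People use a 0–100% slider in their own way, and resting heart rate, skin-conductance level and skin temperature differ between people. A pooled regression without a nurse term does two things wrong with such data.

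First, it counts every rating as an independent observation, although the between-nurse part of each slope rests on only 12 people. Standard errors and p-values come out too small.

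Second, each coefficient becomes a blend of two associations: whether nurses with a higher heart rate report more stress, and whether a given nurse reports more stress when that nurse's heart rate is up. The article's interest, stated under Strengths and Limitations, is in stress patterns from moment to moment, which is the second. The blend can hide a real within-nurse signal, or produce one that reflects only who the 12 nurses are. The Digitally Identifying and Minimizing Stressors section names the correlation between physiological and subjective stress as a study aim, and Future Directions intends to derive preventive measures from the results.

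**Working it through.** The article gives no power, alpha or effect size for this model ("A power analysis was not conducted as the population was prespecified (N=18"), so there is no stated figure to reproduce.

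**Ratings per nurse.** Inputs from the article: 12 nurses, 6 weeks, every shift, two mandatory EMAs per shift, and the inclusion criterion "their working time had to have a minimum of 20 hours per week". Assumptions: 8-hour shifts, a 40-hour week for full time, and every mandatory prompt answered.

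- At 20 h/week: 20/8 = 2.5 shifts; 6 × 2.5 × 2 = 30 ratings per nurse; 12 × 30 = 360 in all.
- At 40 h/week: 40/8 = 5 shifts; 6 × 5 × 2 = 60 ratings per nurse; 12 × 60 = 720 in all.

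Optional EMAs add to this by an amount the article does not state.

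**Understatement of the standard error.** With m ratings per nurse, the variance of a pooled slope is understated by roughly 1 + (m − 1) × ICC(x) × ICC(y), and the standard error by the square root of that. The ICCs are assumptions, shown as a range.

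- m = 30, ICCs 0.1/0.1: √(1 + 29 × 0.01) = √1.29 = 1.14
- m = 60, outcome/predictor ICCs 0.4/0.5: √(1 + 59 × 0.20) = √12.8 = 3.58

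**Simulation of the planned model.** 12 nurses, six mutually independent predictors, no true association, nominal two-sided 5%. The false-positive rate is per coefficient.

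| Ratings per nurse | ICC outcome/predictor | Pooled regression | SE too small by a factor of | After centring within nurse |
|---|---|---|---|---|
| 30 | 0.1/0.1 | 8% | 1.1 | 5% |
| 30 | 0.2/0.2 | 15% | 1.4 | 5% |
| 30 | 0.4/0.5 | 41% | 2.4 | 5% |
| 60 | 0.1/0.1 | 11% | 1.2 | 5% |
| 60 | 0.2/0.2 | 25% | 1.7 | 5% |
| 60 | 0.4/0.5 | 54% | 3.3 | 5% |

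Separate runs differ by a point or two; the 60-rating, ICC 0.2 cell came out between 24% and 26%. The simulated SE factors lie slightly below the approximation, which is for a single predictor. If the predictors do not differ between nurses (predictor ICC 0), the pooled rate stays at about 5%.

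**Blending of slopes.** Approximately, pooled slope = ICC(x) × between-nurse slope + (1 − ICC(x)) × within-nurse slope. Take a true within-nurse slope of 0.30 and a predictor ICC of 0.5.

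- Between-nurse slope 0: 0.5 × 0 + 0.5 × 0.30 = 0.15 (simulated 0.17)
- Between-nurse slope −0.30: 0.5 × (−0.30) + 0.5 × 0.30 = 0 (simulated 0.02)

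With a predictor ICC of 0.2 the simulated values are 0.25 and 0.19. The nurse-centred estimate averaged 0.30 in every case.

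**The alternative reading.** If the regression used one mean per nurse, it would have 12 points and six predictors, leaving 12 − 6 − 1 = 5 residual degrees of freedom, and it would address only differences between nurses.

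**The case against.** The article is condensed, and the model gets one sentence. It does not say that ratings are assumed independent; that follows from running the named method as named. The authors plainly know the data are correlated, since the neighbouring ANOVA says so, and the same section speaks of analyses at the individual level. This stands as a caution on wording, but does not remove the point. The individual-level remark concerns which institution handles the data, and the contrast with the ANOVA makes the missing nurse term more noticeable. The article also commits to a specific model, so this is more than a detail left to an analysis plan.

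Three stronger readings are tempting and not supported.

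- A reader might infer that every activity yields a rating, giving several hundred per nurse. At 400 ratings per nurse, false-positive rates of 63–84% and a ninefold understatement of standard errors can be simulated. But activity-end EMAs were optional, and 400 would need about 13 completed EMAs per shift at 5 shifts a week (400/30), which nothing in the article supports.
- A reader might infer that the label cross-sectional conceals the repeated structure. It does not. The same phrase reads "a prospective cross-sectional approach with continuous measurements throughout each workday", and Study Design then gives the 6-week period.
- A reader might infer that the study's main conclusion is at risk. Feasibility is the primary outcome under Potential Outcomes and Impact, correlations are secondary, and no decision rule hangs on this regression.

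**Conclusion.** The point holds. As written, the regression does not fit the article's own data structure: its p-values are not valid, and its coefficients do not isolate the within-nurse association. At the mandatory-prompt count, the per-coefficient error rate runs from modest (8–11% at ICC 0.1) to severe (40–54% at 0.4/0.5), and it would be worse if many optional EMAs were completed.

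These figures rest on assumed ICCs, 8-hour shifts, full completion of mandatory prompts, and no extra correlation within a shift. The problem with the p-values disappears only if ratings or predictors do not differ between nurses. That is implausible for raw heart rate, tonic EDA and skin temperature, and no standardisation is described for this model. Because the analysis is secondary to feasibility, this is a correction to make before the regression is run or reported, not a flaw that undermines the study.

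**What to change.** Replace the plain regression with one that isolates the within-nurse effect. Either of these will do:

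- nurse fixed effects, which is equivalent to centring the rating and each physiological variable on the nurse's own mean; or
- a linear mixed model with a random nurse intercept, nurse-centred predictors and small-sample degrees of freedom.

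Report the within-nurse coefficients as the answer to the question about momentary stress. A random intercept for shift within nurse and a time-of-day term are optional refinements. Nurse-mean terms should be descriptive at most: six of them on 12 nurses leave the same 5 degrees of freedom as above.

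The cost is analysis syntax and a short change of text, with no new data. Confidence intervals will be wider. The Results section reports data collection as finished and expects final results at the end of 2026 or beginning of 2027, so the change can still be made before publication.

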### Burden in Palliative Caregiving

Palliative nurses face many work-related stressors (like interruptions, time pressures, interpersonal conflicts, or shift work, as aforementioned) that are also experienced by other professions in addition to stressors that are unique to taking care of patients who are terminally ill or close to dying. Additionally, they are not able to express their needs, which can also lead to burden as Seibel et al [5] have published in 2024 (see Table 1, adapted from [6]). It is an imminent part of the job—physicians and palliative nurses are confronted with the end of a patient’s life and with patients and relatives facing this stage. Even though nurses in this field choose this sensitive job after careful consideration, it still is an emotional burden to cope with the dying and death of patients for 54% to 68% of nurses in palliative care [6], which is moderated by circumstances (eg, age of the patient, patient and caregiver agony).

**Table 1 table1:** Examples of potential stressors in a palliative care unit (PCU).

Factors	Examples
Team-associated factors	Staff fluctuation among physicians in the PCU Lack of support Lack of appreciation by other professional groups
Patient-associated factors	Young patients’ ages High care effort due to symptoms (eg, wounds, nausea, breathlessness, restlessness) Insufficient symptom control (eg, therapy-resistant pain, insatiable bleeding)
Structural factors	Understaffing High amount of documentation Inadequate education of patients and relatives about the palliative setting by the referring doctor
Personal factors	Ethical conflicts Feeling of being overwhelmed High expectation of one’s own work

Only a few studies have investigated this topic [6-12]. Diehl et al [11] surveyed and compared strains and resources for 149 nurses (34.5% response rate) working in the field of palliative care (in hospitals, hospices, or outpatient care in Germany). In their study, more than one-half of the nursing activities were perceived as heavy burdens, including transferring patients, time pressures, having to care for too many patients per day, handling patients with severe symptoms, and dealing with grief and death. Being surrounded by these topics every working day, nurses are at risk of psychiatric disorders that can accumulate to result in burnout syndrome in 15% to 20% of palliative nurses in home care [12,13].

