### Digitally Identifying and Minimizing Stressors in Palliative Care Study

The DiPa (Digitally Identifying and Minimizing Stressors in Palliative Care) study was conceptualized to use digital technologies (“Di”) to assess the working conditions of and burden on nurses in palliative settings (“Pa”). The study is a joint project of the Fraunhofer Institute for Computer Graphics Research (IGD) Rostock and the University Medical Centre Rostock (UMR) and funded by the State Office for Health and Social Affairs Mecklenburg-Western Pomerania. The study aims to identify correlations between measured objective physiological parameters and subjective perceptions of stress in everyday situations in the palliative care unit (PCU). Therefore, the primary goal is demonstrating the feasibility of identifying stressors in palliative care and measuring stress reactions with wearable devices. With these initial results, stressors and stress can be reduced by developing preventive measures.

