#### Body-Worn Equipment

The results of measured electrodermal activity (EDA), HR, and skin temperature should provide information about an SNS reaction to stress [14]. All these parameters are recordable with the Empatica E4 (Empatica Inc) research wristband. Thus, to measure the physiological stress reaction, we used the commercially available Empatica E4 wristband [27]. The E4 wristband possesses a photoplethysmography sensor and 2 electrodes to measure the galvanic skin response at the wrist. It was used to measure pulse, HRV, EDA, and body temperature (surface). The automatic data preprocessing was bypassed, since this would require sending the sensitive data to an alien server. To circumvent these international servers for reasons of data protection, the code of the E4 had been altered, allowing the extraction of raw data. Raw data were then sent to the smartphone, which is also part of the study’s setup, and stored on the phone’s memory until transferred to a local server. The E4 had no display and thus provided no feedback to the participants that could interfere with or distort the measurement. LEDs provided the necessary feedback on the functionality of the wristband, and additional feedback on functionality (and connectivity) was given in the corresponding smartphone app.

In addition to the LED, allowing event marking (ie, a real-time annotation) via tapping the button deposits a record in the session file. The record included the time of the button press (expressed as a Unix time stamp in UTC), which was synchronized with the initial time of the corresponding session. Feedback on the button press was given both visually (illuminating the LED) and audibly (beeping). The button press was used for 2 purposes: (1) logging an event of subjectively perceived stress (a single button press) and (2) logging the event of disinfecting one’s hands (as this can alter the EDA; 2 consecutive button presses).

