### Strengths and Limitations

The content-related strengths lie mainly in two aspects: the multitude of measurements and the continuous measurement. As for the multitude of measurements, the study can assess all three aspects of the stress phenomenon: the stressors that elicit stress (activities, ambient conditions, noise, and interruptions—measured via smartphone, NFC tags, and Raspberry Pis), the stress reaction in the sense of subjective appraisal and feelings (measured via EMAs on the smartphone), and the stress reaction in the sense of the objective stress reaction (bioparameters, EDA, heart rate, HRV, and temperature measured via sensor hardware).

In addition, the study also features a methodological strength in the unobtrusiveness, interaction, and automation of the measurement devices: the smartphone and the sensor hardware were worn by the participants and were easily accessed. The sensor hardware was linked to the smartphone and sent data automatically; the smartphone in turn sent these data automatically to the server during the times when it was stored and charged in the lockers. This allowed for smooth data acquisition and increased motivation of the participants to collect data over such a long period and while working.

The study apparatus, for example, the use of smartphones or the scanning of the NFC tags, introduces a potential for user fatigue or confusion. The feasibility of sustained use was not assessed in this study, as the study did and does not intend sustained use of the apparatus. The assessment was deliberately limited to a duration of weeks to gain insights on the status quo of perceived stress, with a long-term goal of deducing provisions to reduce stress. However, the level of perceived fatigue caused by the interaction with technological devices, as well as the level of acceptance of technology and skill level when interacting with technology, could be assessed in future studies with a larger sample to allow for analyzing potential influences of these factors.

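### The stress-prediction regression counts acceleration as physiological, so its overall fit could be read as physiological predictability when only movement predicts the rating

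*Protocol article*

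**What the plan says.** The protocol article gives the purpose of the analysis in Data Analyses: "To examine the predictability of experiencing stress, the subjective ratings given in the EMA will be used as ground truth". The model follows: "A linear regression will be computed with the subjective stress level (EMA) as the dependent variable", "entering the means of the physiological variables (HR, HRV, tonic EDA, phasic EDA, temperature, and acceleration) as independent variables". All six predictors carry the same label and enter together. On the preparation of acceleration the section says only this: "The acceleration data were fused to a 3D vector by applying the following equation" (the equation itself is not reproduced in the text at hand). It gives acceleration no role as a movement covariate and describes no comparison with a movement-only model.

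The regression serves an aim given in the Introduction, in the section on the DiPa study: "The study aims to identify correlations between measured objective physiological parameters and subjective perceptions of stress".

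Elsewhere the bodily stress reaction is described without acceleration. Body-Worn Equipment has: "The results of measured electrodermal activity (EDA), HR, and skin temperature should provide information about an SNS reaction to stress". Strengths and Limitations has: "the objective stress reaction (bioparameters, EDA, heart rate, HRV, and temperature measured via sensor hardware".

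**The concern.** By the article's own scheme, stressors (which include activities) are one thing and the bodily reaction another. Movement belongs nearer to activity. It can follow the rating through workload alone: in Burden in Palliative Caregiving, the activities that a cited survey found to be heavy burdens are described as "including transferring patients, time pressures, having to care for too many patients per day", among others. Under Questionnaires, most momentary ratings are prompted when an activity ends, for example on leaving a patient room, so recent movement is likely to fall in the data window.

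A model with acceleration among its predictors can therefore fit for two different reasons: busier nurses move more and rate their stress higher, or the body shows a stress reaction that the wristband detects. Only the second answers the question about physiological parameters. Predictability is naturally read from whole-model fit, and that fit does not tell the two apart. With all six predictors labelled physiological, a respectable R-squared could be taken as support for wearable stress measurement when no stress marker contributed to it.

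**Working it through.** **The lists side by side (protocol article).**

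| Section | Signals named | Acceleration? |
|---|---|---|
| Data Analyses, regression | HR, HRV, tonic EDA, phasic EDA, temperature, acceleration | yes, as physiological |
| Body-Worn Equipment, sympathetic reaction | EDA, HR, skin temperature | no |
| Body-Worn Equipment, use of the wristband | pulse, HRV, EDA, surface temperature | no |
| Strengths and Limitations, objective reaction | EDA, HR, HRV, temperature | no |

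The neural network inputs in Future Directions also omit acceleration. They omit HR and temperature too, so that list is weak evidence.

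**No figure to reproduce.** The article states no number of ratings, alpha, power or R-squared for this regression. What follows is an illustration.

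**Assumptions, none from the documents.** Ratings are independent. The rating depends on acceleration only, with correlation r = 0.1, 0.2 or 0.3. HR correlates with acceleration at c = 0 or 0.5, and the other four signals are pure noise. There are n = 200 or 1000 ratings, tests are at 5%, and each setting has 2000 simulated studies. The Monte Carlo standard error at a 5% rate is √(0.05 × 0.95/2000) = 0.005, or half a percentage point.

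**Formulas.** TSS is the total sum of squares. RSS1 is the residual sum of squares with acceleration alone, and RSS6 with all six predictors.

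- Overall test: F = [(TSS − RSS6)/6] / [RSS6/(n − 7)].
- Joint test of the five bodily signals given acceleration: F = [(RSS1 − RSS6)/5] / [RSS6/(n − 7)].
- Increment in R-squared: (RSS1 − RSS6)/TSS.

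**Results (percentage of studies significant; mean R-squared).**

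| n | r | c | Overall, six | Five given acceleration | Acceleration coefficient | HR coefficient | R² full | Increment | Five, acceleration dropped |
|---|---|---|---|---|---|---|---|---|---|
| 200 | 0.1 | 0 | 15.3 | 5.4 | 29.1 | 5.0 | 0.040 | 0.025 | 5.2 |
| 200 | 0.1 | 0.5 | 13.7 | 4.3 | 22.4 | 5.3 | 0.040 | 0.025 | 6.9 |
| 200 | 0.2 | 0 | 53.6 | 4.5 | 80.7 | 5.1 | 0.069 | 0.024 | 4.8 |
| 200 | 0.2 | 0.5 | 51.7 | 4.3 | 68.1 | 4.6 | 0.067 | 0.024 | 14.3 |
| 200 | 0.3 | 0 | 91.8 | 4.8 | 99.0 | 4.3 | 0.116 | 0.023 | 5.0 |
| 200 | 0.3 | 0.5 | 92.5 | 4.3 | 95.9 | 4.3 | 0.117 | 0.023 | 32.6 |
| 1000 | 0.1 | 0 | 63.5 | 5.2 | 87.2 | 5.3 | 0.016 | 0.005 | 5.2 |
| 1000 | 0.1 | 0.5 | 63.5 | 4.5 | 77.3 | 5.6 | 0.016 | 0.005 | 18.4 |
| 1000 | 0.2 | 0 | 100 | 5.3 | 100 | 5.6 | 0.046 | 0.005 | 5.5 |
| 1000 | 0.2 | 0.5 | 100 | 4.1 | 100 | 4.4 | 0.045 | 0.005 | 68.7 |
| 1000 | 0.3 | 0 | 100 | 4.9 | 100 | 4.2 | 0.096 | 0.005 | 4.3 |
| 1000 | 0.3 | 0.5 | 100 | 5.3 | 100 | 5.5 | 0.096 | 0.005 | 97.6 |

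**Hand check of one setting (n = 200, r = 0.3).** The expected full R-squared is about 1 − (1 − 0.09) × 193/199 = 0.117. The expected increment of five predictors that carry nothing is about 0.91 × 5/199 = 0.023. Both agree with the table, so the increment there is pure chance.

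**Reading.** The overall test follows movement and ranges from 14% to 100%. The joint test of the bodily signals stays at 4% to 5%. The last column shows that dropping acceleration is no remedy: where HR correlates with movement, HR carries the movement effect.

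**The case against.** A reader might infer that a movement-only fit is bound to be reported as stress being predictable from physiology. The article does not support that. Its stated purpose is the predictability of stress, without the addition that it is from physiology. It makes neither the overall R-squared nor the overall F test the criterion. All six predictors are named openly, and a linear regression also gives a coefficient for each. In the illustration the HR coefficient is significant in only 4% to 6% of studies and the acceleration coefficient in 22% to 100%, so a coefficient table would show the source. All of this stands, and it limits the point to what could be read from the overall fit.

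A reader might also infer that acceleration should be removed. That is wrong: its presence protects the other coefficients.

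Three further points have weight. Separate ANOVAs of stressful events against baseline are planned for each physiological parameter, so the physiological claim does not rest on this regression alone. The primary outcome is feasibility, and correlations are secondary. The overview under Apparatus speaks of physical as well as psychological stress, so movement is not wholly foreign to the subject. Even so, none of this makes the overall fit a measure of what HR, HRV, EDA and temperature contribute.

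The illustration assumes that only movement matters, so it shows the mechanism and not how likely it is. The cited survey does not show that wrist acceleration follows momentary ratings. Independence is also unrealistic for repeated ratings from 12 nurses.

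Finally, order of entry and nested tests are often left to an analysis plan that is not at hand. Their absence alone would be no finding. What the article does fix is the label and the single pooled predictor set.

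**Conclusion.** The point holds in a limited form. The regression labels a movement measure physiological, against the article's own descriptions of the bodily stress reaction. As stated, its overall fit cannot separate movement from bodily signals, so it cannot by itself answer whether physiological parameters follow perceived stress.

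The size is unknown from the documents. Under the assumptions listed, with no bodily effect beyond movement, the overall test is significant in about 14% of studies at the weak end (r = 0.1, 200 ratings) and in all of them at the strong end (r = 0.2 or more, 1000 ratings). The joint test of the five bodily signals keeps its nominal 5%. These percentages depend on the assumed correlations, number of ratings and independence, and are not a forecast for this study.

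This is a cheap improvement to a secondary analysis. It does not show that the planned model is invalid or that its results will be misreported.

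**What to change.** Name acceleration a movement covariate and keep it in the model. Fit the regression in two blocks: acceleration first, then HR, HRV, tonic EDA, phasic EDA and temperature. Base any statement on physiological predictability on the second block's change in R-squared and its joint test, and show the acceleration-only and full-model fits beside it.

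The cost is one extra model on data already collected. The downside is that signal shared by movement and physiology is credited to movement, so the increment is a conservative figure and should be described as such. Showing all three fits lets the reader see how much is at stake in that choice.
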